## Abstract

**Background:**

Progresses in childhood cancer treatment, diagnosis, and management have resulted in childhood cancer survival rates of over 80%. However, this therapeutic success comes with a heavy price: two-thirds of childhood cancer survivors will be affected by further complications, including cardiovascular and metabolic diseases. Adequate nutrition during cancer treatment is essential to ensure the child’s optimal development, improve tolerance to treatments, and can contribute to lower the risk of developing cardiometabolic diseases. Side effects of cancer treatments can negatively impact children’s nutritional intake and eating behaviors. Involving the families of childhood cancer patients in educational workshops could be a promising avenue to promote healthy eating during and after cancer treatment.

**Objective:**

The objectives of this study were to develop, validate, and implement a family-based nutrition education and cooking workshop curriculum in a pediatric oncology setting that addresses the nutritional issues encountered during treatments while promoting the adoption of healthy eating habits for the prevention of long-term cardiometabolic effects.

**Methods:**

The workshops were developed and validated following an 8-step iterative process, including a review of the literature and consultations with a steering committee. An evaluation tool was also developed. A nonrandomized study protocol was elaborated to implement the workshops and measure their impact. The themes of the 6 research- and practice-based lessons are as follows: meal fortification during cancer treatment, changes in taste during cancer therapy and their impact on children, adapting diet to eating-related side effects of treatments, nutritional support during cancer treatment, Mediterranean diet and health, and planning quick and economic meals. The validation process included consultations with the institution’s clinical nutrition professionals. Self-administered post questionnaires were developed according to the content of each workshop to measure short-term outcomes, namely, participants’ perception of knowledge acquisition, behavioral intention, and satisfaction. Medium-term outcomes that will be evaluated are participants’ anthropometric profile, quality of the diet, and circulating biomarkers of metabolic health.

**Results:**

The project was funded in 2016 and enrollment will be completed in 2021. Data analysis is currently under way and the first results are expected to be submitted for publication in 2019.

**Conclusions:**

This research- and practice-based nutrition education and cooking demonstration curriculum could be a valuable complement to a multidisciplinary lifestyle intervention for the prevention of long-term cardiometabolic complications in childhood cancer.

## Introduction

### Long-Term Health Complications in Childhood Cancer Survivors

Progresses accomplished in childhood cancer treatment, diagnosis, and management in the past decades have led to survival rates exceeding 80% [1,2]. Despite these encouraging statistics, it is estimated that about two-thirds of childhood cancer survivors (CCS) will be affected by treatment-related long-term complications [3], including cardiovascular and metabolic diseases [4,5]. Lifestyle practices such as healthy eating and physical activity are well-recognized modifiable factors that contribute to lower the risk of cardiometabolic complications [6]. Particularly, adherence to a Mediterranean dietary pattern has been associated with reduced risk factors related to the metabolic syndrome in survivors of childhood acute lymphoblastic leukemia [7]. In addition to the prevention of long-term sequelae, good nutrition is essential to ensure children’s requirements for growth and development during cancer treatments. Adequate nutritional status is also associated with increased tolerance to cancer treatments, better prognosis, and enhanced quality of life [8]. Side effects of cancer treatments such as nausea, mucositis, taste disorders, poor appetite, or increased appetite secondary to steroids intake can impact children’s eating behaviors and nutritional status [8]. Furthermore, it is known that eating habits acquired in childhood are likely to persist in adulthood [9,10] and after completion of cancer treatments [11].

### Children’s Dietary Habits During Cancer Treatment

Studies on CCS have described similar dietary habits to those of the general population, reflecting a suboptimal diet for the prevention of metabolic syndrome components such as obesity, insulin resistance, arterial hypertension, or dyslipidemia [12]. So, involving families of children with cancer to adopt or maintain healthy habits during and after cancer treatment is essential. Moreover, given that parents often experience time constraints [13] and economic burden related to transportation, accommodation, or loss of work income [14], practical advice for meal preparation should be provided to meet families’ needs. Design and evaluation of family-based nutrition and cooking education programs are increasingly reported in the literature, mainly related to the prevention or management of childhood obesity [15-19]. Nutritional interventions for young CCS and their families have been described in the literature [20-22], but, to our knowledge, only few were developed for children undergoing cancer treatment and those that were targeted patients in the maintenance phase of therapy [23-25]. As there is a need to develop and evaluate the feasibility of an early intervention during the course of pediatric cancer treatments, we have developed 6 nutrition and cooking education workshops that aim to increase knowledge relative to the following: (1) children’s nutrition during and after cancer treatments; (2) healthy, quick, and economical food preparation, cooking techniques, and food safety specific for children with cancer; and (3) development of food preferences during childhood and parental feeding practices. Here, we describe the following: (1) the development and validation of the workshops; (2) the elaboration of an evaluation tool; and (3) the study protocol to implement the workshops and to measure their impact.

## Methods

### Setting

We have developed a protocol for a nonrandomized controlled study. This study has been developed within the VIE (Valorization, Implication, Education) Program at the Sainte-Justine University Health Center (SJUHC) in Montreal, Canada. This research program consists of a 4-year family-oriented multidisciplinary interventional program integrating physical activity, nutrition, and psychosocial clinical and research teams. The nutritional intervention includes personalized assessment, goal setting, and counseling for behavioral changes with a registered dietitian (RD) as well as group nutrition education and cooking workshops providing complementary information. The SJUHC Institutional Review Board approved the study, and investigations will be carried out in accordance with the principles of the Declaration of Helsinki.

### Curriculum Development and Validation Process

The research- and practice-based curriculum consists of 6 lessons developed by a team of researchers and RD and validated by the hematology-oncology clinical nutrition team at SJUHC. The workshops are designed to provide reliable, up-to-date nutritional information geared to address specific themes and associated to cooking demonstrations facilitated by a RD and a chef.

To develop the curriculum, evidence for common nutritional and behavioral eating problems related to side effects of childhood cancer treatment and their management has been reviewed in the scientific literature published between 2000 and 2017 contained in Medline, PubMed, and Scopus databases. A few core papers published before 2000 have also been considered. Gray literature was searched for Canadian governmental guidelines and family-oriented documentation related to children’s diet while on cancer treatment published by recognized organizations, such as the Children Oncology Group and the Canadian Cancer Society. Insight from the SJUHC Centre de cancérologie Charles-Bruneau (CCCB) clinical nutrition team has also been sought. Recipes for demonstration were developed and standardized to match each of the 6 lesson themes. Nutritional value of recipes was analyzed based on general (for protein, lipid, and sodium content) and theme-specific criteria and was inspired by those of the SJUHC institutional food service, of early childhood nutrition reference [26], and of the Heart and Stroke Foundation program [27].

The curriculum was validated concurrently with its development within an 8-step process (Figure 1). The first 6 steps have already been completed. Subsequent to the literature review, primary themes and specific lesson objectives were elaborated and submitted to a steering committee, composed of SJUHC CCCB clinical RD (n=2) and the Department head of the Clinical Nutrition Services, representing, respectively, 19, 15, and 10 years of experience in pediatric oncology. A consensus on improvements to be made was obtained, and a detailed content of the lessons was then elaborated based on current scientific evidence and common practices by the clinical nutrition team. The modified and detailed content was submitted to the clinicians for a second validation, followed by a final revision of the curriculum. Workshops were pretested with nonparticipants, including CCCB health care professionals, leading to further refinements.

Subsequent steps will be performed before official implementation and intervention evaluation. A validation meeting will be conducted with a committee composed of family members and CCS to better tailor the curriculum regarding the length of the workshop, the timing, and the amount of information delivered. After implementation, we will continually monitor the curriculum and evaluation tools to fine-tune and optimize content delivery.

### Curriculum Description and Content

The developed curriculum consists of 6 themed workshops with specific objectives and key messages (Table 1). The 6 lessons are independent from one another, and there is no specific sequence to attend the workshops. This will increase convenience and allow flexibility according to participants’ schedule and needs for information. The nutritional criteria of the recipes are presented in Table 2.

The curriculum will promote a liberalized diet that reinforces food safety guidelines for immunocompromised patients based on Health Canada food safety guidelines for people with a weakened immune system [61] and in line with the SJUHC CCCB standard clinical practices. Patients receiving hematopoietic cell transplantation will be referred to the hematology-oncology RD for personalized diet and food safety guidelines.

**Figure 1 figure1:**
[figure not shown]
The 8-step development and validation process of the VIE (Valorization, Implication, Education) Program educational workshops. The dotted line divides the steps that have been completed and those to be performed.

**Table 1 table1:** Themes, objectives, and evidence-based key messages of the nutrition education and cooking workshops.

Lesson theme	Specific objectives	Learning objectives (specific key messages)
Meal fortification during cancer treatment	Understand the role and importance of proteins, calcium, and vitamin D Learn strategies to fortify usual foods with these nutrients	Proteins are essential for tissue growth and repair and to support immune system function [28,29] A source of protein should be included in every meal [30] Calcium, vitamin D, and proteins are essential for bone growth and play a role in secondary osteoporosis prevention [31,32]
Changes in taste during cancer therapy and their impact on children	Understand the development of taste and food preferences in children Learn strategies to enhance the flavor of food and to improve meal acceptability during cancer treatment Understand positive parental feeding practices for optimal taste development and eating behaviors	Food aversion, neophobia, need for routine and security, need for self-expression, and learning from social modeling are normal behaviors related to the development of taste in children [9,33]. These behaviors can be affected by cancer treatments [34,35] Parental strategies and attitudes can influence adherence to a healthy diet in children during and after treatments. These include promoting participation in meal preparation when possible [36], maintaining a pleasant atmosphere during meal times, proposing a variety of food, and offering a mealtime structure (where, when, what), while letting the child decide the amount and select the foods from the offering [33] Some herbs, spices, and acidic food can enhance the flavor of dishes and can be used to mask the perceived metallic taste [37,38]
Adapting diet to eating-related side effects of treatments	Learn how to adapt the child’s diet to improve food intake when mucositis, nausea, or vomiting are present Learn strategies to attenuate diarrhea and constipation secondary to cancer treatments	Nausea during treatments can be a side effect of the treatment and can be caused by a metallic or a medication taste in the mouth (dysgeusia) [39,40] Strategies to adapt diet and promote oral intake when the child is experiencing mucositis include serving warm meals and nonirritating foods with soft and moist texture [41] Soluble fibers, notably psyllium, can be helpful for diarrhea, whereas insoluble fibers and concentrated sugars should be limited [42,43] Total dietary fibers promote intestinal regularity and help prevent constipation [43]
Nutritional support during cancer treatment	Demystify oral, enteral, and parenteral nutritional support to facilitate their acceptability by patients and families Understand positive parental feeding practices during nutritional support	Nutritional support is an adjuvant to cancer treatment in situations when the child’s needs are not met with oral eating alone [44,45] When allowed by the medical team, presentation of food to the child should be encouraged during nutritional support [46,47] Some strategies can facilitate acceptation of nutritional support [36,48]
Mediterranean diet and health	Learn approaches to integrate principles of the Mediterranean diet into usual meals Learn the benefits of adherence to a Mediterranean diet for the whole family	The Mediterranean diet brings health benefits to the whole family, especially for the prevention of cardiovascular diseases [49,50] The adherence to a Mediterranean diet can be improved with small changes daily (eg, adding a portion of vegetables to usual meals, replacing refined grains by whole grains) [7] Vegetal and animal proteins offer different health advantages: it is beneficial to diversify protein sources [51,52] The use of vegetable oils (nonhydrogenated) is preferred to butter or shortening [53,54]
Planning quick and economic meals	Learn planning strategies to remove barriers to cooking at home Learn tactics to prepare simple and quick meals using accessible and nutritious ingredients Acquire strategies for eating healthy on a budget	Meal planning saves time and reduces daily stress [55,56] Keeping some essential foods in the pantry, fridge, and freezer helps to prepare last-minute balanced meals [57] Low-cost alternatives can be found in several food categories [58,59]
		
		

**Table 2 table2:** Nutritional criteria for recipes of the nutrition education and cooking workshops.

Lesson theme	Nutritional criteria^a^
Meal fortification during cancer treatment	Recipes rich in proteins that include at least one calcium-rich and one vitamin D-rich ingredient Protein: >20 g for a meal and >10 g for a snack Calcium: >165 mg for a meal and >0 mg for a snack Vitamin D (if possible): >15% of the adequate intake: 90 UI (2.25 mg)
Changes in taste during cancer therapy and their impact on children	Recipes include ingredients to enhance the taste of dishes (eg, herbs or spices) while limiting sodium and dietary fat and include ingredients to mask metallic taste (eg, acidic ingredients like lemon juice or vinegar)
Adapting diet to eating-related side effects of treatments	Recipes for nausea include: Cold or warm meals that release less odor Ingredients to enhance taste and mask metallic taste, such as herbs, spices, or acidic ingredients Recipes for diarrhea include: Meals without irritants (eg, strong spices, insoluble fiber) Soluble fibers: >2 g Limited in concentrated sugar: <5 g for a meal and <2 g for a snack Recipes for constipation include: Fiber-rich ingredients (eg, whole grains, vegetables, fruits) Total fibers >4 g Recipe for mucositis include: Dish with a soft and moist texture Without irritants (eg, strong spices, acidic ingredients, salt) Can be reduced in puree if needed Served at room temperature
Nutritional support during cancer treatment	Recipes rich in proteins (>20 g for a meal and >10 g for a snack) Meal or snacks also include complex carbohydrates and healthy fats
Mediterranean diet and health	Fish as the main ingredient Recipes include whole grains and vegetables, or suggest them as side dishes Include healthy fats (eg, canola or olive oil, nuts or seeds, avocado)
Planning quick and economic meals	Recipe includes 2 pantry essentials and costs less than Can $4 per portion

^a^Nutritional criteria are based on adult portions. Parents will be advised to adapt the portion served according to the child’s usual appetite. According to the Satter Eating Competence Model, the parent decides the type of food served while letting the child decide the amount based on his or her internal cues [33,60].

### Study Protocol

#### Recruitment of Participants and Controls

From January 2018 to December 2020, parents and children newly diagnosed with cancer, treated at the SJUHC, and meeting the inclusion criteria will be offered to participate in the VIE Program. Participant recruitment will be sequential. Inclusion criteria are as follows: (1) being less than 21 years old at diagnosis, (2) being treated with radiotherapy or chemotherapy (including patients receiving hematopoietic cell transplantation), and (3) able to give an informed consent (by parents or legal tutors). Participants who are not receiving radiotherapy or chemotherapy will be excluded from the study. Patients will be followed for 4 years. On average, 140 children per year are admitted at the SJUHC’s CCCB, of which about 110 would be eligible. On the basis of earlier studies, we expect an average of 75 patients recruited per year (70.0% recruitment rate), for a total of 150 participants over 2 years. Enrolled participants and their family (parents, grandparents, etc) will be encouraged to attend the nutrition education and cooking workshops. It is to the parents’ discretion to attend workshops with or without the child, according to the child’s age, interest, and health condition. The control group will be recruited sequentially from patients diagnosed at the CCCB 3 to 4 years ago, who were not exposed to the VIE Program and who fulfill the same inclusion criteria as for the intervention group. No intervention will be offered to control participants. The measures and questions used will be the same as for the end-of-protocol intervention in the patients from the intervention group.

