### Considerations Related to Childhood Cancer

Further studies need to evaluate the feasibility of implementing workshops for pediatric oncology patients undergoing cancer treatments. The moment surrounding the diagnosis and treatment of cancer has been described as a *teachable moment* for a healthier lifestyle in adult cancer [82]. However, this opportunity window is not well documented in children. Families overwhelmed with the diagnosis might be less interested or find it too challenging to adopt healthy habits while experiencing a distressing life event [83]. However, focus groups with parents of overweight CCS testing a 6-lesson curriculum after completion of their child’s treatment revealed that some would have preferred to receive the intervention earlier in the process [67], supporting that the timing of our intervention might be optimal.

The heterogeneity of the target population, which comprises children of various ages, diagnoses, and treatments, was a challenge in the development of the curriculum. Evaluating the implementation of the workshops will inform us on participation rate and will allow to calculate sample size of future nutrition education and cooking program in pediatric oncology. The nonrandomized design is also a limitation of this study. Our study was designed to ensure that every newly diagnosed patient could participate and benefit from this novel lifestyle study. Therefore, control participants will only be recruited among patients who completed the standard treatment before the VIE Program was implemented.

We are confident that this intervention will contribute to increase knowledge about nutrition and cooking in the context of childhood cancer. Hopefully, it will improve children’s diet quality while promoting long-term healthy eating habits to prevent cardiometabolic complications. This research- and practice-based nutrition education and cooking demonstration curriculum will be a valuable complement to the VIE Program lifestyle intervention for the prevention of cardiometabolic long-term complications.

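### The article defines the control group in two different ways; the narrower rule selects controls on treatment length and leaves the between-group comparison open to bias, of a size that depends on unstated control recruitment dates

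*Protocol article*

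**What the plan says.** Under Recruitment of Participants and Controls, intervention patients are enrolled when newly diagnosed: "From January 2018 to December 2020, parents and children newly diagnosed with cancer" are invited, and "Patients will be followed for 4 years". For controls the same section says: "The control group will be recruited sequentially from patients diagnosed at the CCCB 3 to 4 years ago". Two further conditions, absence of VIE exposure and shared inclusion criteria, complete that definition. It does not require their treatment to be over. Their assessment is tied to the end of the intervention: "The measures and questions used will be the same as for the end-of-protocol intervention in the patients from the intervention group".

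Under Considerations Related to Childhood Cancer, the explanation of the nonrandomized design adds a condition: "control participants will only be recruited among patients who completed the standard treatment before the VIE Program was implemented".

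Under Workshop Evaluation Tools and Outcome Measurement, diet quality and the anthropometric and biochemical profiles are to be compared with this control group. It is the only between-group comparison that the article describes.

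**The concern.** A patient 3 to 4 years from diagnosis who is still on treatment, or who finished after VIE began, is an eligible control under the Methods and is barred by the Discussion. Staff cannot tell which rule to apply.

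The choice matters because the Discussion's condition selects on treatment length in one group only. Intervention patients enter at diagnosis, before anyone knows when their treatment will end. The Introduction itself attributes long-term complications to treatment and says that treatment side effects change eating behavior. Control and intervention groups that differ in treatment length could therefore differ in diet, anthropometry and metabolic markers without any effect of the program. Controls are described as having only the end-of-protocol measures, so the article gives no earlier value against which to correct them.

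A smaller question is the clock: 3 to 4 years from diagnosis for controls, against the end of a 4-year follow-up for intervention patients.

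**Working it through.** The article gives no figure for control selection, so there is none to reproduce. The check sets the rules side by side and follows the calendar.

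**Inputs from the article.** Controls are diagnosed 3 to 4 years before recruitment (Methods). Their treatment ended before VIE was implemented (Discussion). Intervention follow-up is 4 years (Methods).

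**Assumptions.** VIE opened at V = January 2018, the start of participant recruitment; January 2017 was also tried. Diagnosis dates are uniform within the window. Treatment lengths and control recruitment dates are not in the article and are varied.

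**Step 1. Cap on treatment length.** A control recruited at date R was diagnosed between R − 4 and R − 3. Treatment must have ended before V, so the longest admissible treatment is V minus the diagnosis date, which runs from V − R + 3 to V − R + 4 years. For an assumed treatment length L, the share of the window that passes is min(1, max(0, V − L − (R − 4))).

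| Control recruited | Longest admissible treatment (years) | Share passing, L = 0.5 | L = 1 | L = 2 | L = 2.5 | L = 3 |
|---|---|---|---|---|---|---|
| January 2018 | 3 to 4 | 1 | 1 | 1 | 1 | 1 |
| January 2019 | 2 to 3 | 1 | 1 | 1 | 0.5 | 0 |
| January 2020 | 1 to 2 | 1 | 1 | 0 | 0 | 0 |
| January 2021 | 0 to 1 | 0.5 | 0 | 0 | 0 | 0 |
| January 2022 | nobody qualifies | 0 | 0 | 0 | 0 | 0 |

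With V = January 2017 each limit is one year shorter, and nobody qualifies from January 2021.

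**Step 2. Effect on case mix (illustration).** Suppose that 40% of intervention patients have long treatment (2.5 years) and 60% short (0.5 years), and that controls are recruited evenly from January 2018. The admissible length is D − T, with D uniform on 3 to 4 years and T uniform over the control recruitment period.

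- Three years of recruitment: P(D − T ≥ 2.5) = E[(D − 2.5)/3] = 1/3 = 0.333. For short treatment, half the D range gives an average of 2.75/3 = 0.917 and the other half gives 1, so P = 0.958. Long-treatment share among controls = 0.4 × 0.333 / (0.4 × 0.333 + 0.6 × 0.958) = 0.188.
- Two years: the probabilities are 0.5 and 1; share = 0.20 / (0.20 + 0.60) = 0.250.
- One year: the probabilities are 0.875 and 1; share = 0.35 / (0.35 + 0.60) = 0.368.

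Against 40% in the intervention group, controls would have about 19%, 25% or 37%.

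**Step 3. Time since diagnosis.** The gap is 4 years minus 3 to 4 years, that is 0 to 1 year, with mean 0.5. If enrolment follows diagnosis by an assumed 6 months, intervention patients are measured at 4.5 years and the gap is 0.5 to 1.5 years.

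**The case against.** The strongest reply is that the Discussion's rule narrows the Methods rule rather than contradicting it. That stands: a patient diagnosed 3 to 4 years ago whose treatment ended before VIE meets both. A reader might infer a flat contradiction from the requirement of the same inclusion criteria, since one criterion is "being treated with radiotherapy or chemotherapy (including patients receiving hematopoietic cell transplantation" and the section adds: "Participants who are not receiving radiotherapy or chemotherapy will be excluded from the study". Read at the moment of control recruitment, this would bar everyone whom the Discussion requires. The natural reading, however, is treatment for the index cancer, and on that reading the rules are compatible, though different.

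Second, the size of the effect rests on dates that the article does not give. The January 2018 to December 2020 window is for intervention patients. If controls are recruited within about a year of VIE opening, 37% against 40% is negligible. This also stands. One could further read 3 to 4 years ago as a cohort fixed at one date, with no moving window. That removes the tightening but worsens the timing: with January 2018 as the reference date (diagnosis January 2014 to January 2015), a control recruited in January 2020 would be 5 to 6 years from diagnosis.

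Third, age, diagnosis, age at diagnosis, treatment protocol and socio-economic status are collected, and an adjustment plan may sit in documents not shown. A reader might infer that the comparison is confounded and that nothing corrects it; the article does not support so strong a statement. Even so, adjustment cannot supply long-treatment controls whom the rule has removed, nor settle which rule was applied.

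Fourth, the completion rule plausibly guards against exposure, since patients still treated at the center could meet the posters and staff promotion. The criterion of no exposure to VIE already addresses this, provided that it is verified. Finally, the article concedes that the design is nonrandomized, but it names neither treatment length nor time since diagnosis.

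**Conclusion.** The two definitions admit different patients and must be reconciled. As written, the Discussion's condition selects controls, but not intervention patients, on treatment length. This leaves the between-group comparison open to bias; it does not show that bias is present. The effect is negligible if all controls are recruited within about a year of VIE opening and strong if they are recruited from 2020, assuming that VIE opened in January 2018. The case-mix percentages are illustrations that also rest on assumed treatment lengths and an assumed 40% share. The difference in time since diagnosis is secondary: 0 to 1 year, about 0.5 on average, with the two clocks meeting at 4 years if there is no enrolment delay.

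This is worth correcting before controls are recruited, because selection cannot be undone afterwards. It does not undermine the whole study: the short-term workshop evaluation (perceived knowledge, intention, satisfaction) uses no controls, and the analysis by workshop attendance can be made within the intervention group.

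**What to change.** 1. State one control rule in both places: diagnosed before VIE opened, verified as not exposed to it, and meeting the same inclusion criteria, with treatment defined as treatment for the index cancer. State the VIE opening date and the control recruitment dates.
2. Drop the completed-treatment condition, or apply the same on- or off-treatment status at measurement to both groups.
3. Compare at the same time since diagnosis, either by assessing controls at about 4 years or by using an intervention visit in the 3-to-4-year window.
4. Adjust the comparison for diagnosis, treatment protocol and age, which are already collected.

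The cost is a few sentences of protocol text and an adjusted model. Narrowing the window makes the control pool slightly smaller; a one-year window holds about 110 eligible patients if past admissions matched the article's figure. Non-exposure must be checked in controls still treated at the center. With diagnosis required before an assumed January 2018 opening, the 3-to-4-year window loses no one until January 2021 and is empty from January 2022, so control recruitment must be finished by then.
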